### Data collection clinics

Primary and secondary outcome data are collected at baseline and 12 months (when participants attend data collection clinics) and some are also collected at six months (paperwork is sent and returned by post). Baseline data are not collected until eligibility has been confirmed and the participant has given written informed consent.

Clinics are held at the two hospital sites or at local community venues and are staffed by appropriately trained research nurses and healthcare assistants. All clinical measures are carried out in accordance with study-specific standard operating procedures (SOPs) in place at the two sites and standard calibrated equipment is used. Participants are given a £15 gift voucher for every data collection clinic or education session they attend as a contribution towards childcare costs. If the session is held in a venue where childcare is available, the cost is paid by the study budget and the participant does not receive a voucher.

### Randomisation and blinding

Study identification numbers are assigned sequentially and participants are individually randomised (1:1) stratified by age (< 30 years; ≥ 30 years) and ethnicity (White European; other) using a variable block size after their baseline assessment. The randomisation schedule was developed by an independent statistician and allocation of randomisation is carried out by a researcher based in Leicester who is independent of the team. Randomisation determines which group the participant is allocated to (control or intervention). After randomisation, participants in both groups are sent a letter informing them of the outcome of the randomisation. In addition, intervention participants are contacted by telephone to discuss the dates available for them to attend the Baby Steps programme. They are then sent a letter confirming the venue and dates and times of the programme. Since the intervention is a group self-management programme, participants and the local research teams cannot be blinded to the randomisation. The staff analysing the accelerometer data to derive the primary outcome are blinded to allocation.

### Treatment regimens

#### Control group

Control group participants are sent an information booklet about the prevention of diabetes.

#### Intervention group

Participants randomised to the intervention group are invited to participate in the Baby Steps programme. This has two components: a group-based structured education programme and a secure mobile web application which provides access to information and learning tools to supplement the group programme.

The group programme is based on Let’s Prevent Diabetes and Walking Away from Diabetes, group education programmes which have been shown to be effective for people at increased risk of developing T2D [38, 39]. They are based on robust theoretical frameworks and the philosophy is based on patient empowerment [40–42]. The Baby Steps programme comprises two group sessions that are each 3 h long and are delivered approximately two weeks apart. A total of 8–10 people are booked to attend each programme and are given the opportunity to bring a friend or member of the family if they wish. Session 1 focuses on the background to GDM and being at risk of T2D, physical activity and other modifiable risk factors and goal setting (Table 1). The second session revisits physical activity and reviews progress on goals, barriers and solutions and then covers diet and food choices with goal setting relating to reducing risk of developing T2D. The programme is delivered in a facilitative style that encourages participation with the use of reflective questioning and problem-solving activities to promote engagement. The education sessions are delivered at the two hospital sites as well as at local community venues. The target is to attend within two months of recruitment. However, a pragmatic approach is taken and this is not always possible. A sensitivity analysis will be performed to take this into account.

**Table 1 Tab1:** Contents of the Baby Steps group education programme

Session 1	Session 2
Introduction and housekeeping (5 min)	Welcome back (5 min)
Your story (25 min)	Sharing stories (30 min)
Blood glucose (20 min)	Revisiting physical activity (15 min)
How could being at risk of diabetes affect my health? (15 min)	Weight management (30 min)
Risk story (25 min)	Food choices (45 min)
Being more active (70 min)	Planning to reduce my risk (30 min)
Reflections (5 min)	Questions and future care (10 min)
TOTAL - 2 h 45 min (+ 15 min break) = 3 h	TOTAL - 2 h 45 min (+ 15 min break) = 3 h

During Session 1, participants are given a secure link to a mobile web application which has been developed to accompany the programme. The application has two main functions: first, to provide an interactive education component to follow on from the group component; and second, to motivate the user into becoming more active. It contains a variety of resources of different formats (e.g. video animations, expert videos, interactive activities and quizzes) which supplement the messages delivered during the group sessions. In addition, there are booster sessions (released monthly for nine months) which contain further information and challenges. Participants are given a wrist-worn activity monitor that can connect to the website using a human application programming interface (API). Regular automated messages are sent in relation to goal setting, goals achieved and the setting of new challenges with daily updates and motivational messages. Participants can opt to join a group who can use the website to share their challenges and experiences with their peers. More information on the application is provided in Additional file 2.

Development of the group education programme followed an iterative pathway comprising various stages of design, testing and refining the programme [43]. It was developed by a multidisciplinary team with substantial co-production from patient and public involvement (PPI) and other stakeholder groups (including midwives and maternity care assistants). Four meetings were held with stakeholders (two with women who had previously had GDM and two with healthcare professionals). The discussions were led by an independent and experienced qualitative researcher from the University of Leicester and informed on content of the programme, the online resource and practical issues such as the number of sessions, ideal venues and times of the day, and whether the session should be limited to women. The interactive website is hosted on a safe secure server and was developed in collaboration with a web designer with healthcare professionals and patient groups involved at all stages. An iterative pathway similar to that used in the development of the group programme was followed.

A small team of facilitators has been trained in each site. They are either appropriately skilled lay people or healthcare professionals. They attended a two-day training programme at the beginning of the study. The first day covered the facilitator skills needed and the theories and models underpinning the programme. The second day covered the curriculum content and ensured they were familiar with the teaching resources used in its delivery. Facilitators were given a curriculum and set of teaching resources and delivered a ‘have a go’ session to volunteer patients before the study started. These practice sessions were observed by a member of the training team and feedback and further training was provided as needed. Continued mentoring and peer support are provided to the facilitators and self-reflection and peer reflection after every session is encouraged.

### Outcome measures

#### Demographics and medical history

The participant’s age, ethnicity, smoking and alcohol status, and number of children are recorded. Details of any relevant history of disease and medications and first-degree family history of diabetes are recorded. Figure 2 summarises the outcome data which will be collected at each study visit.

#### Primary outcome

The primary outcome measure is change in objectively measured physical activity from baseline to 12 months using the GENEActiv wrist-worn tri-axial accelerometer (GENEActiv model 1.1, ActivInsights Ltd., Cambridgeshire, UK) with a dynamic range of ± 8 *g*, where *g* is equal to the Earth’s gravitational pull. Participants are asked to wear the GENEActiv accelerometer on their non-dominant wrist for eight consecutive days (24 h), wearing the monitor from the date of the assessment visit or from a specified date when sent in the six-month postal follow-up. The accelerometer is initialised to collect data at 100 Hz. An appropriately trained individual instructs the participant on correct placement of the monitor. Participants are asked to complete a log while wearing the accelerometer to provide their waking hours and wear time information. Participants are given a prepaid envelope to return the accelerometer and log book once completed. Accelerometer data will be calibrated and analysed according to best practice procedures through the Lifestyle Theme of the NIHR Leicester Biomedical Research Centre. In brief, data will be processed and calibrated using a bespoke open source package in R (GGIR http://cran.r-project.org according to criteria previously described [44–46]. Data will be included if participants have one or more valid days of data, with a valid day defined as at least 16 h of wear time. The primary outcome is defined a priori as overall movement intensity as quantified by the Euclidean Norm minus 1 *g* (ENMO) method. In addition, time asleep, sleep quality, time in sedentary behaviour, light-intensity physical activity and moderate to vigorous physical activity will also be derived using validated algorithms and thresholds.

#### Secondary outcomes

##### Clinical and anthropometric measures

Blood pressure and resting pulse rate are measured after the participant has been sitting for 5 min. Three measurements are made; the first measurement will be excluded when calculating the mean. Body weight (kg) and height (m) are measured and used to calculate BMI (weight in kg/m^2^). Waist circumference (cm) is measured at approximately 1 cm above the iliac crest and hip circumference (cm) at the widest area around the gluteus maximus.

##### Blood tests

Venous blood samples for analysis of non-fasting HbA1c and full lipid profile (total cholesterol, LDL cholesterol, HDL cholesterol and triglycerides) are collected at baseline and 12 months by trained personnel. They are analysed in accredited laboratories at University Hospitals of Leicester NHS Trust or at George Eliot Hospital NHS Trust in accordance with their SOPS and are destroyed after analysis. All laboratory results are reviewed and the reports signed by the Principle Investigator at each site or an individual approved by the Chief Investigator in the Delegation of Authority log. The results are recorded in the clinical record form (CRF) and identified as normal, abnormal but not clinically significant, or abnormal and clinically significant. In case of the latter, the eligibility of the participant to continue on the study is reviewed.

Participants may optionally consent to provide blood samples of serum, plasma and whole blood, which will be stored indefinitely for future ethically approved research. At the end of the study, the samples from George Eliot Hospital will be transported to University Hospitals of Leicester using an accredited courier service and stored in a Human Tissue Act licensed laboratory in line with all relevant agreements in place.

##### Questionnaire data

Participants are asked to complete the following questionnaires at baseline, 6 and 12 months. They are given in person at the baseline and 12 months clinics and sent by post at 6 months.Recent Physical Activity Questionnaire (RPAQ): the RPAQ is designed to explore day-to-day physical activity levels in the previous four weeks. The questionnaire comprises three sections: (1) physical activity patterns in and around the house; (2) travel to work and work activities; and (3) recreational activities. RPAQ has reasonable validity for measuring total physical activity levels [47, 48].Health-Related Quality of Life EuroQoL (EQ-5D-5 L): the EQ-5D-5 L assesses health-related quality of life and provides useful data for health economic analyses. It is a validated measure of health status and has five quality of life dimensions (mobility, self-care, usual activities, pain/discomfort and anxiety/depression) which are all coded in the range of 1–5 [49].Jenkins self-efficacy for exercise expectations scale: this validated self-efficacy scale measures ability to exercise when considering nine barriers. These are weather, boredom, pain, exercising alone, lack of enjoyment, busyness, tiredness, stress and depression [50].Hospital Anxiety and Depression Scale (HADS): HADS is a validated scale measuring the severity of symptoms of anxiety and depression. It comprises 14 statements of which seven relate to anxiety and seven relate to depression [49]. Each statement has an option of four responses scored in the range of 0–3. Upon completion the scores selected are totalled and reported for anxiety and depression individually.Fruit and Vegetable intake questionnaire: the Five-A-Day Consumption and Evaluation Tool (FACET), which is recommended by the Department of Health, is used as a measure of fruit and vegetable intake [51] .

### Sample size

The primary outcome is based on increasing total physical activity as quantified by the Euclidean norm minus one (ENMO) method measured in milligravity units (m*g*). This is the main measure of activity derived from the GENEActiv monitor. In order to detect a minimum clinically significant difference of 2.1 m*g*, which is equivalent to an overall increase in physical activity volume of approximately 30 min of light walking at 4 km/h, assuming a standard deviation of 5.3 m*g* [52], a power of 80% and significance level of 5%, the sample size requires 202 participants. To allow for 20% loss to follow-up and 10% non-compliance of the GENEActiv monitor, we will need to recruit 290 participants (145 in each arm).

### Statistical analysis

Descriptive characteristics at baseline will be summarised by treatment arm. Numbers (with percentages) for binary and categorical variables and means (and standard deviations) or medians (with lower and upper quartiles) as appropriate for continuous variables will be presented. Preliminary graphical and tabular presentations of the data will be inspected for the correct statistical modelling assumptions.

The primary analyses will use a complete case population. For the primary outcome (change from baseline in total physical activity), treatment arms will be compared using linear regression with a binary indicator for randomisation group as the explanatory variable, terms for the stratification factors as confounders, and adjustment for the change in accelerometer wear time and baseline total physical activity. Sensitivity analyses will include a per-protocol analysis (defined as attending at least one of the two group education sessions, i.e. those randomised to intervention but not attending either group session will be excluded) and an intention-to-treat analysis where missing data will be imputed using multiple imputations. Interaction effects will be fitted between intervention arm and age (< median vs ≥ median), and ethnicity (White European vs other). If the interaction term is statistically significant then stratified analyses will be performed for that factor using the same model as the primary analyses. Secondary outcomes will be analysed using similar methods as the main analysis, with an appropriate model selected dependent on the distribution of the outcome.

The results of all comparative analyses will be presented with 95% confidence intervals and statistical significance for main effects will be assessed at the 5% level. All *p* values shown will be two-sided. Statistical significance for interaction effects will be assessed at the 10% level.

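### The intervention is taught in groups of 8–10, but the primary regression and the sample size treat all women as independent; if outcomes within groups are positively correlated, the standard error is understated

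*Protocol article*

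**What the plan says.** All references are to the protocol article.

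- **Randomisation and blinding:** "participants are individually randomised (1:1) stratified by age" and ethnicity. The unit of allocation is the woman.
- **Control group:** an information booklet, with no group contact.
- **Intervention group:** two 3-hour facilitated sessions about two weeks apart. "A total of 8–10 people are booked to attend each programme". A web application, an activity monitor and an opt-in online peer group follow. A small team of facilitators at each site delivers the sessions.
- **Sample size:** difference 2.1 mg, SD 5.3 mg, 80% power, 5% significance; on these inputs "the sample size requires 202 participants", raised to 290 (145 per arm) for 20% loss to follow-up and 10% monitor non-compliance. No ICC or design effect appears.
- **Statistical analysis:** "treatment arms will be compared using linear regression with a binary indicator for randomisation group as the explanatory variable", plus the covariates. All p values are two-sided. The sensitivity analyses named there are per-protocol and multiple imputation; the Intervention group section adds one for late attendance. None concerns education group.

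**The concern.** This is a partially nested design: individually randomised, with one arm taught in groups and the other ungrouped. Women in the same programme share facilitators, venue, timing, fellow participants, and joint problem-solving and goal setting. Any of these could make their 12-month activity more alike than that of women in different programmes.

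Ordinary linear regression assumes no such similarity. If it exists and is positive, the model-based standard error of the arm difference is too small, the 95% interval covers less than 95%, and the 5% test rejects too often. The primary p value and interval will decide whether the programme is called effective and put forward for primary care. The estimated difference itself is not shown to be biased; only its stated precision is in question.

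The article names both the model and the sample size inputs, so this is a stated choice and not a detail left to a later plan.

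**Working it through.** **1. Reproduce the plan's figure.** Inputs from Sample size: δ = 2.1, σ = 5.3, 80% power, α = 0.05. Statistical analysis makes tests two-sided.

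- Normal approximation: n per arm = 2 × [(1.960 + 0.8416) × 5.3 / 2.1]² = 99.99, so 100 per arm.
- Two-sample t test: 101 per arm gives power 80.0% (100 gives 79.6%). Total 202, as stated.
- Attrition: 202 / 0.70 = 288.6, so 289 against the stated 290.

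Both figures follow from independent observations, so they hide no clustering allowance.

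**2. Group sizes.** 145 / 10 = 14.5 and 145 / 8 = 18.1, so roughly 15–18 programmes. With the planned 30% loss, a programme of 9 leaves 9 × 0.70 = 6.3 analysed. Both m = 6.3 and m = 9 (no loss) are shown.

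**3. Formulae.** Clustering is in one arm only, with equal arms and equal total variance:

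- DE = 1 + (m − 1) × ICC
- true variance / assumed variance: R = (1 + DE) / 2
- true type I error of the planned test = 2 × [1 − Φ(1.960 / √R)]
- power of a test using the correct standard error = Φ(2.816 / √R − 1.960), where 2.816 = 2.1 / (5.3 × √(2/101))

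The ICC is not in the documents; 0.01 to 0.10 is an assumed range.

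**4. Results** (before any credit for baseline adjustment; the power formula gives 80.4% at ICC 0)

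| m | ICC | DE | R | √R | Type I error | Power |
|---|---|---|---|---|---|---|
| 6.3 | 0.01 | 1.053 | 1.027 | 1.013 | 5.3% | 79.4% |
| 6.3 | 0.05 | 1.265 | 1.133 | 1.064 | 6.6% | 75.4% |
| 6.3 | 0.10 | 1.530 | 1.265 | 1.125 | 8.1% | 70.7% |
| 9 | 0.01 | 1.080 | 1.040 | 1.020 | 5.5% | 78.8% |
| 9 | 0.05 | 1.400 | 1.200 | 1.095 | 7.4% | 72.9% |
| 9 | 0.10 | 1.800 | 1.400 | 1.183 | 9.8% | 66.3% |

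Worked line (m = 6.3, ICC 0.05): DE = 1 + 5.3 × 0.05 = 1.265; R = 2.265 / 2 = 1.1325; √R = 1.064; 1.960 / 1.064 = 1.842, giving 6.6%; 2.816 / 1.064 − 1.960 = 0.686, giving 75.4%.

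**5. Credit for baseline adjustment.** The planned model adjusts for baseline activity, but the sample size takes no credit for it. If 5.3 mg is the SD of a single measurement and the baseline-to-12-month correlation is ρ (not given; assumed), the residual SD is 5.3 × √(1 − ρ²). At ρ = 0.5 the factor is 0.866. It is the same if 5.3 mg is the SD of change, because at ρ = 0.5 the two SDs coincide.

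| m | ρ | ICC 0.01 | ICC 0.05 | ICC 0.10 |
|---|---|---|---|---|
| 6.3 | 0.5 | 89.4% | 86.3% | 82.4% |
| 9 | 0.5 | 89.0% | 84.3% | 78.5% |
| 6.3 | 0.3 (single-measurement SD) | 83.0% | 79.2% | 74.7% |

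The baseline covariate scales the true and the model-based standard error alike. For a given ICC of the adjusted outcome, R and the type I error column in step 4 do not change.

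**The case against.** A reader might infer from the group delivery that the intervals are too narrow and that 80% power is not delivered. The documents do not support either as fact. They give no ICC, and at 0.01 the error rate is about 5.3–5.5%, which nobody would act on. The power inference also overlooks the baseline adjustment in the planned model: at an assumed ρ of 0.5 and about 6 per group, power stays above 80% across the whole ICC range. This objection stands, so both consequences must be worded conditionally.

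Features of the trial may also keep the ICC low. Group contact is two sessions, the outcome is measured at 12 months, and the continuing components (monitor, automated messages, monthly web boosters) are mainly individual. The online peer group is optional and is not said to match the education group, so it is weak support for clustering by programme. Women who attend neither session have no group exposure. These are fair reasons to expect a modest ICC, not evidence that it is zero.

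Finally, a random-intercept model is one choice among several, and with 15–18 small groups it is not obviously superior to cluster-robust errors. That stands too, so the fix leaves the method open. None of this answers the main point: if the ICC is positive, nothing in the planned analysis corrects the standard error.

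**Conclusion.** The point holds in conditional form. The plan teaches one arm in groups and fixes a primary model and a sample size that both assume independence. If outcomes within education groups are positively correlated, the nominal 5% test has a true error of about 5.3% to 8.1% with about 6 analysed per group, or 5.5% to 9.8% with 9, over assumed ICCs of 0.01 to 0.10. The effect is negligible at the low end and material from about 0.05.

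These figures assume equal arms and group sizes, equal total variance, and clustering in the intervention arm only; applying a design effect to the whole trial would exaggerate the problem. Loss of power is possible but unproven, since it depends on an unstated ICC and an unstated baseline correlation. This should be fixed, but it does not invalidate the design.

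**What to change.** 1. Record the booked programme identifier for every intervention participant. Booking letters are already sent, so the information should exist.
2. In Statistical analysis, keep the same fixed effects and make the primary analysis account for education group in the intervention arm. Use either a partially nested mixed model (random intercept for programme in that arm only, with Satterthwaite or Kenward-Roger degrees of freedom) or cluster-robust errors with a small-sample correction. Controls and never-booked women are singletons. Define groups by the programme booked, because attendance is selective; some booked women will not have attended.
3. In Sample size, state that 80% power assumes no clustering. Show power over a range of ICCs: about 79%, 75% and 71% at 0.01, 0.05 and 0.10 with about 6 analysed per group, before any credit for baseline adjustment. Add that baseline adjustment may recover this power but does not correct the type I error or the interval width.

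The cost is one recorded field and some wording, with no extra recruitment. The downside is a possibly wider confidence interval; if the ICC is near zero, the result should barely change.

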The ongoing and completed intervention programmes for women with a history of GDM have been conducted largely in women of white American, Australian or European background [19, 23, 31, 32] and black, Hispanic and mixed minority American [24, 33–35]. Therefore, there is a paucity of information about the feasibility and effectiveness of similar programmes for women in the UK, particularly in those of South Asian ethnicity. It is known that up to one in five South Asian adults globally have T2D and the diagnosis is 4–5 times more common in South Asian adults in the UK, compared to a white reference group [36, 37].

Our study will therefore be novel in developing and testing an intervention that meets the cultural and social needs of women in a catchment area in that has a large multi-ethnic population (estimated to constitute 25–60% of the women diagnosed with GDM in the two research sites).

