### Study design and setting

The study is a two-group (1:1), parallel RCT of women who have had GDM during any pregnancy up to 60 months before the point of recruitment and are therefore at risk of developing T2D. Figure 1 describes the flow of participants through the study. The RCT is being conducted in two sites in the UK, namely University Hospitals of Leicester NHS Trust (serving the catchment area of Leicester City and the county of Leicestershire) and George Eliot Hospital NHS Trust (serving the catchment area of North Warwickshire). The protocol was written in accordance with the Standard Protocol Items: Recommendations for Interventional Trials (SPIRIT) guidelines (see Spirit Fig. 2 and the SPIRIT Checklist, which is available as Additional file 1). The study is sponsored by the University of Leicester and ethical approval was granted by the East Midlands – Derby Research Ethics Committee. The study was prospectively registered (ISRCTN 17299860).

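### Site is neither stratified on nor in the stated model: a minor, nearly free precision gain is left unused, most clearly for HbA1c and lipids

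*Protocol article*

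**What the plan says.** Under Study design and setting, "The RCT is being conducted in two sites in the UK": Leicester, with its city and county, and George Eliot Hospital, serving North Warwickshire. Under Randomisation and blinding, allocation is individual and "stratified by age (< 30 years; ≥ 30 years) and ethnicity (White European; other) using a variable block size". Site is not among the factors.

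Under Statistical analysis, the primary model for change in activity contains arm, "terms for the stratification factors as confounders", change in accelerometer wear time and baseline activity. Secondary outcomes use similar methods, with the model suited to the distribution of the outcome. Site is not a term.

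Three other places show where the sites may differ:

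- Blood tests, on the HbA1c and lipid samples: "They are analysed in accredited laboratories at University Hospitals of Leicester NHS Trust or at" the George Eliot trust.
- Background, on the multi-ethnic population: "estimated to constitute 25–60% of the women diagnosed with GDM in the two research sites". The split by site is not given.
- Intervention group: "A small team of facilitators has been trained in each site".

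The accelerometer data behind the primary outcome are processed in one Leicester centre by one method (Primary outcome).

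**The concern.** In a two-site trial, site is a baseline factor known for every woman. It stands in for population, local services, clinic staff and, here, the laboratory. When it is neither stratified on nor fitted, two things follow. Whatever part of the outcome varies by site, beyond what ethnicity and the baseline value explain, stays in the residual and widens the confidence interval. And the arms can differ by chance in their site mix without the model correcting for it.

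Precision is what is at stake, not validity. It matters most for the laboratory outcomes, because for those site also identifies the measuring instrument.

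**Working it through.** **Inputs from the protocol article (Sample size).** Target difference 2.1 mg (milligravity), SD 5.3 mg, two-sided 5%, power 80%, 202 evaluable, 290 recruited after allowing 20% + 10%.

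**Assumed, because the article does not give them.** The smaller site's share of women p; the between-site difference in mean change d; the share of residual variance R² explained by site.

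**1. The plan's own figure.** Normal approximation: n per arm = 2(1.960 + 0.842)² × 5.3² / 2.1² ≈ 100, or 200 in total. With the noncentral t it is 101 per arm = 202 (power 80.02%). Then 101 / 0.70 = 144.3, rounded up to 145 per arm = 290. Both stated figures reproduce.

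**2. Chance imbalance by site.** With no restriction by site, the SD of the between-arm difference in site share is √[p(1 − p) × 2/101]. At p = 0.25 this is √(0.25 × 0.75 × 2/101) = 0.061, so the 95% range is about ±12 percentage points. Stratifying by ethnicity may narrow this a little. The shift in the treatment estimate is 1.96 × SD × d:

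| p | SD of imbalance | d = 1 mg | d = 2.1 mg |
|---|---|---|---|
| 0.1 | 0.042 | ±0.08 mg | ±0.17 mg |
| 0.5 | 0.070 | ±0.14 mg | ±0.29 mg |

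For scale, the standard error of the treatment difference is 5.3 × √(2/101) = 0.75 mg. These shifts average zero over randomisation and are already part of the standard error.

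**3. Gain in standard error.** The ratio with and without site is √(1 − R²): √0.98 = 0.990 and √0.95 = 0.975, a fall of about 1% to 2.5%. To see what this assumes, R² = p(1 − p)d²/5.3². At p = 0.25, R² = 2% needs d = √(0.02 × 28.09/0.1875) = 1.7 mg, and R² = 5% needs d = √(0.05 × 28.09/0.1875) = 2.7 mg. So the assumed 2–5% already implies a site difference close to or above the target effect.

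**4. Gain in power at 101 per arm (80.4% by the normal approximation), for p from 0.1 to 0.5.**

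| d | 5.3 includes site variance: power with site fitted | 5.3 is within-site: power with site omitted |
|---|---|---|
| 0.5 mg | 80.4–80.5% | 80.3–80.4% |
| 1 mg | 80.5–80.7% | 80.0–80.3% |
| 2.1 mg | 80.9–81.9% | 78.9–79.8% |
| 3 mg | 81.5–83.5% | 77.3–79.3% |

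**5. Price of the term.** If site explains nothing, its chance correlation with arm inflates the variance by about 1/202 = 0.5%, which is 0.25% on the standard error.

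**6. Laboratory outcomes.** Suppose one laboratory reads higher by a constant δ at both visits, and each woman's two samples go to the same laboratory. In a model for change adjusted for baseline, with slope β of the 12-month value on the baseline value, the site difference left over is δ − βδ = (1 − β)δ. For an assumed β of 0.5 to 0.8, 50% to 20% of the offset remains. A drift in one laboratory between the visits is not removed at all.

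**The case against.** The strongest reply is that a model matched to the factors used in randomisation, plus the baseline value, is the standard choice, and that further covariates can wait for the analysis plan. The first half stands: the test and interval are valid without site. The second half stands for detail such as the content of the imputation model, which is not raised here. It does not cover the primary model, whose terms the article lists in full.

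Three stronger readings are tempting, and the article does not support them.

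- *That site variation is known.* No passage reports a site difference in activity, HbA1c or lipids, or the number of women per site. The accelerometer data are handled centrally. The ethnic mix is partly covered by the White European/other term, and stable differences in activity partly by the baseline term.
- *That the omission biases the result.* Women are individually randomised, so imbalance by site has expectation zero. It is imprecision.
- *That a site term would absorb the clustering of women within education groups.* Facilitators and groups exist only in the intervention arm. A difference between facilitator teams is therefore a site-by-treatment effect, which a main effect fitted across both arms does not represent. It also does nothing for groups within a site.

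For HbA1c and lipids, both laboratories are accredited and a baseline value is available, which reduces the problem. By step 6 it does not remove it.

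**Conclusion.** The point holds as a minor, nearly free improvement. Site is absent from both the stratification and the stated model, and nothing in the article explains why. The size is small and conditional. The standard error falls by about 1–2.5% if site explains an assumed 2–5% of residual variance. Power changes by about 1.5 points or less unless the sites differ in mean change by more than 2.1 mg. If the sites barely differ in activity change, the primary analysis gains nothing and loses almost nothing. The better argument concerns HbA1c and lipids, where site marks the laboratory and part of any offset survives baseline adjustment. The size of such an offset is not documented.

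**What to change.** Pre-specify site as a fixed covariate in the primary model and in the secondary-outcome models, alongside the age and ethnicity strata. If the sponsor prefers to keep the primary model as it stands, fit site at least for HbA1c and lipids and in a site-adjusted sensitivity analysis of the primary outcome.

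The cost is one degree of freedom out of about 200. Randomisation, visits and data collection are untouched. Recruitment was still open when the article was published (Trial status), so at that stage the term could be fixed before the outcome data were analysed.
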